### Qualitative evaluation

The qualitative research will increase the understanding of the process of implementation within the environment in which the interventions take place. Focus groups (FGs) have been chosen to investigate the perspectives of care staff within the setting in which the interventions will be tested. The aim of FGs is to encourage the type of interaction that would occur in everyday life but with greater focus, and to allow the researchers access to ideologies, practices and desires among specific groups of people. Engaging groups of care staff in discussion of their current work and new therapeutic approaches is also likely to increase their collaboration in the research programme. Staff beliefs, attitudes and behaviour in their work with people with dementia are key components of this context. Recognition and acknowledgement of staff perspectives is also essential to negotiating the implementation of the interventions.

The first phase of the qualitative evaluation will be undertaken in the care homes (residential and nursing homes) participating in the intervention study, prior to the commencement of the intervention. The pre-intervention groups at the sixteen participating care homes will consist of eight to twelve members of the care staff, including the two lead members of the care staff who are to be trained to assist with the implementation of the intervention. Evidence from the systematic review will provide the initial themes to be explored in the FGs. Potential issues may, for example, include staff time to implement interventions and management support. The topic guide will be revised iteratively to include new themes emerging from the FGs. Participants will be encouraged to discuss their work with residents with dementia, their perceptions of residents’ quality of life, unmet needs and ways to improve these, the potential benefits of the intervention and their own role in implementation. The aims and content of the specific interventions will be considered.

The FGs will be repeated at the end of the pilot study to explore participants’ experiences of the interventions and any changes in their views. The researcher will provide a summary of the FG’s first discussion and seek feedback on interpretation and any changes in views post intervention. They will be asked to discuss positive and negative outcomes, obstacles and facilitators in delivering the intervention. Their views on refining the interventions will be sought. All group discussions will be audio-recorded and transcribed verbatim.

### Intervention fidelity

To monitor intervention fidelity, each therapist will be required to videotape at least two interventions and/or planning sessions. In addition, the type and frequency of interventions will be determined through audit of an intervention log completed by the therapist; audit of detailed intervention plans describing each intervention undertaken; audit of care plans; and a supervision log. In particular, given that there is a degree of overlap between the social interaction and pleasant activities intervention and the exercise intervention, it will be especially important to ensure that the exercise intervention specifically promotes exercise-based activities and to clearly profile the similarities and differences in these two intervention packages.

### Economic evaluation

The economic evaluation in this pilot study will focus on the amount of staff time needed and the overall cost of each intervention, as well as the patterns of service use for individual residents and the associated costs. It will do this by collecting information on the current living arrangements (including usual place of residence and other places of residence); followed by questions about any use the participant may have made of a range of hospital, community-based and day services (both health and social care) over a defined retrospective period. These data on service contacts, staff time and costs will be examined alongside data on outcomes to help preparation for the main study later in the WHELD programme.

### Inclusion, exclusion and withdrawal criteria

#### Home selection: inclusion, exclusion and withdrawal criteria

Eight care homes will represent a convenience sample (block 1) of local care homes, already known to the research team, which meet the inclusion and exclusion criteria and have previously expressed a willingness to participate in research. The other eight care homes will be identified from all care homes in the research area rated as ‘adequate’ or better on the Care Quality Commission (CQC) register (block 2). All care homes listed in the CQC register that meet the study’s inclusion and exclusion criteria will be entered into a study database. Next, this list of eligible care homes will be randomised and the homes approached in the order of appearance on the randomised list. If a care home declines to participate the next care home on the list will be approached.

Care homes scored adequate or better on the CQC register will be eligible for inclusion. Care homes in which 60% or fewer of the residents have dementia, and care homes receiving special support from a local authority will be excluded.

### Participant selection: inclusion, exclusion and withdrawal criteria

All residents who potentially eligible for evaluation will be identified by the care home staff. The inclusion criteria will be individuals residing in participating care homes and meeting the diagnostic criteria for dementia, a score of 1 or greater on the Clinical Dementia Rating Scale (CDR) [25], and a score of 4 or greater on the functional assessment staging (FAST) [26]. Any resident for whom consent is not obtained will be excluded. In terms of withdrawal criteria, individual participants would be able to withdraw from the study evaluation at any time.

### Staff selection: inclusion, exclusion and withdrawal criteria

All staff working in participating care homes would be potentially eligible to participate in the FGs as part of the qualitative evaluation. Consent for their participation will be sought separately. They will be excluded if consent is not obtained and are able to withdraw from the study at any time.

### Assessment and follow up

Assessments will be made pre-baseline to assess the suitability of the care homes for inclusion, as shown in Table 1. This process will include assessments to identify the total number of participants likely to be eligible for screening. Participants will be screened and consent obtained prior to baseline evaluation and to randomization of the care homes. Follow up assessments will be made nine months after commencement of the intervention.

**Table 1 T1:** Outcome and study eligibility measures

	**Domain**	**Purpose**	**How long to complete**	**Who completes**	**Pre-BL**	**BL**	**Ongoing**	**Post-int**
**Measures of home**								
Number and approximate proportion of residents with dementia	Demographic	Eligibility	1 hour - records search and informant interview	Researcher	Y			Y
Rating on CQC criteria	Demographic	Eligibility	15 mins - records search	Researcher	Y			Y
**Measures of individual**								
Demographics	Demographic	Demographics	10 mins - records search and informant interview	Researcher		Y		Y
Functional assessment staging (FAST) [26]	Diagnostic criteria	Eligibility	15 mins trial assessments and informant interview	Researcher	Y			Y
CDR [25]	Diagnostic criteria	Eligibility	15 mins - trial assessments and informant interview	Researcher	Y			
Antipsychotic use (number and proportion of people and dose)	Medication use	Quantitative	5 mins per resident - records search and drug chart	Researcher		Y		Y
		Primary outcome						
Use of other psychotropic drugs (No. and proportion of people and dose)	Medication use	Quantitative	5 mins per resident - records search and drug chart	Researcher		Y		Y
		Secondary outcome						
Cohen-Mansfield agitation inventory (CMAI) [27]	Agitation	Quantitative	10 mins	Researcher with staff		Y		Y
		Primary outcome						
Neuropsychiatric inventory - nursing home version (NPI-NH) [28]	Other behavioural and neuro-psychiatric symptoms including apathy and psychosis	Quantitative	20 mins	Researcher with staff		Y		Y
		Secondary outcome						
Cornell depression scale [29]	Mood	Quantitative	10-15 mins	Researcher with staff and residents		Y		Y
		Secondary outcome						
Rating anxiety in dementia (RAID) [30]	Mood	Quantitative	10-15 mins each	Researcher with staff and residents		Y		Y
		Secondary outcome						
Camberwell assessment of need in the elderly (CANE) [31]	Unmet needs	Quantitative	30 mins each	Researcher with staff and residents		Y		Y
		Secondary outcome						
Assessment of QoL for people with dementia (DEMQOL) [32]	Quality of life (QoL)	Quantitative	20 mins each	Researcher with staff and separately with residents		Y		Y
		Secondary Outcome						
QoL in Alzheimer’s disease (QoL-AD) [33]	Quality of life	Quantitative	5-10 mins	Researcher with staff and separately with residents		Y		Y
		Secondary Outcome						
Quality of interaction schedule (QUIS, observational tool) [34]	Quality of interactions between staff and residents	Quantitative	2 hours observation per home	Researcher		Y		Y
		Secondary Outcome						
Falls record	Falls	Quantitative	5 mins	Care staff			Y	
		Secondary outcome						
Case examples	Skills and attitude development	Qualitative		Researcher	Y			
Implementation process		Qualitative		Researcher	Y			
Staff time		Economic		Researcher			Y	
**Economic measures**								
Client service receipt inventory [35]	Information on service contacts	Economic	45 mins	Researcher			Y	
Administrative records	Cost of intervention	Economic		Researcher				Y

CQC, Care Quality Commission; QUIS, quality of interaction schedule; BL, Baseline; Pre-int, Pre-intervention; Y, Yes.

### Data management and analysis

It is planned that anonymous data and all appropriate documentation will be kept securely for a period of seven years following the completion of the trial, subject to discussion with relevant Ethics Committees.

### Quantitative data management

Administrative databases will be held at the study centre. All participants and care homes will be identified by a unique study number; this number will be used to tag all research data sent outside the study centre, for example to North Wales Organisation for Randomised Trials in Health Clinical Trials Unit (NWORTH CTU). Quantitative research data will be entered via a web interface to the MACRO research databases held at NWORTH. Primary data management will be conducted by the research team in the study centre, and the secondary cleaning and preparation of the data for analysis will be conducted by NWORTH.

### Quantitative data analysis

With the exception of the quality of interaction schedule (QUIS) observational study, which is conducted at a group level, all outcome data will be collected at an individual level for the individual participants. Outcome measures for pilot evaluation will be assessed at baseline and nine months and are listed in Table 1. All the outcome measures collected will be described and reported using appropriate descriptive statistics, tabular and graphical techniques. Particular note will be taken of baseline SDs and overall effect sizes. These data will be used to inform power calculations for Work Plan 5 (WP5). The change from baseline in the PCC group will quantified and fully described.

The CONSORT diagram information will be assessed to identify potential differences in dropout rates and other data quality issues in order to inform the design of WP5. A more detailed statistical analysis plan will be drawn up prior to analysing the data, which will be approved by the programme steering group and the Data Monitoring and Ethics committee.

The analysis of outcomes will involve a multilevel analysis of variance (ANOVA) model for the 2 × 2 × 2 factorial design with two replications among the care homes and participants, clustered within each care home. The three factors being examined are the presence or not of antipsychotic review, of social interaction and of exercise. The two replications refer to the two lists of care homes, those previously known and those not known to the investigators. Means with 95% confidence intervals will be quoted and a 5% significance level will be reported. As this is a hypotheses-generating pilot study, no adjustment will be made for multiple comparisons.

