### Hypotheses

Each intervention will significantly improve several key outcomes but none when used alone will improve all outcomes. This pilot randomised trial is not powered to provide a definitive answer but to guide the analysis and to generate firm hypotheses for testing in a definitive large-scale cluster randomised trial.

Specifically the hypotheses are that compared to person-centred care alone are:

1. PCC plus antipsychotic review will result in the reduction of antipsychotic prescribing.

2. PCC and social interaction with pleasant activities will result in reductions in agitation/aggression, especially in individuals already experiencing these symptoms at the baseline evaluation.

3. PCC and exercise will improve mood and reduce falls.

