## Methods/Design

### Overall design

The study design is a cluster-randomised, 2 × 2 × 2 factorial design (with two replications), pilot study in 16 care homes, as shown in Figure 1. Each cluster includes a minimum of 12 participants (depending upon the size of the care home, the number of people with dementia and the number consenting). Each cluster receives a randomly allocated intervention for a minimum of nine months. Evaluations will be undertaken to understand the breadth of benefits conferred by three key interventions to be assessed when used in addition to the person-centred care training package, where efficacy has already been established. The flow chart for the research is shown in Figure 2.

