### Number of participants and power of the study

Sixteen suitable care homes to be identified, recruited and randomised, with the intervention delivered to all residents, with a minimum recruitment target of 12 individuals with dementia per care home. All residents within the care homes, who meet the study’s eligibility criteria will be invited to participate, which will help to account for the potential loss of participants during the course of the study. Baseline and follow up data will be collected on all consenting residents who meet the inclusion criteria at each participating care home. This is an exploratory pilot study whose main purpose is to collect data to enable the design and sample size calculation for the definitive RCT. As such, the size of effect for the outcome measures, their SDs and intra-class correlations (ICCs) are unknown.

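### The outcome model is named as a multilevel ANOVA with no baseline term, although every outcome except falls has a baseline value; adjusting for it would give more precision at very little cost

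*Protocol article*

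**What the plan says.** The protocol article, Quantitative data analysis, gives the model class: "The analysis of outcomes will involve a multilevel analysis of variance (ANOVA) model". It then gives the terms: "The three factors being examined are the presence or not of antipsychotic review, of social interaction and of exercise", with replication defined as the two lists of homes (known and not known to the investigators) and residents clustered within homes.

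Baseline appears in that section only in descriptive roles: attention to baseline SDs, and a description of change from baseline in the PCC group. No baseline covariate is named, and the response variable (nine-month value or change) is not defined. A more detailed statistical analysis plan is to follow.

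Table 1 marks eleven measures as primary or secondary outcomes. Ten are scheduled at baseline and after the intervention, including both primaries (antipsychotic use and CMAI). Falls are recorded only as ongoing.

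Under Hypotheses, hypothesis 2 expects social interaction to reduce agitation, "especially in individuals already experiencing these symptoms at the baseline evaluation". No analysis in the article is tied to that clause.

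**The concern.** The design has few independent units. Under Overall design, "The study design is a cluster-randomised, 2 × 2 × 2 factorial design (with two replications), pilot study in 16 care homes", so each factor's main effect is a contrast of 8 homes with 8. The only stated constraint on the randomisation concerns geographic location. Nothing balances baseline agitation or prescribing between the two sides of a contrast, so with so few homes a chance difference at baseline can be sizeable, and an unadjusted model leaves it in the estimate.

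The baseline values that would remove much of this variation are already being collected. If the analysis follows the model as named, standard errors will be larger than they need be. This affects the confidence intervals that the article promises and the effect sizes that it intends to use for the WP5 power calculations.

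**Working it through.** **No figure to reproduce.** The article makes no power claim: "This pilot randomised trial is not powered to provide a definitive answer", and "the size of effect for the outcome measures, their SDs and intra-class correlations (ICCs) are unknown". The only design arithmetic is 8 combinations × 2 homes = 16 homes, and 16 × 12 = 192 residents at minimum.

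**Inputs from the article**
- 8 versus 8 homes per main effect (Overall design).
- m = 12 residents per home: "with a minimum recruitment target of 12 individuals with dementia per care home".
- Significance level: "Means with 95% confidence intervals will be quoted and a 5% significance level will be reported", taken as two-sided.

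**Assumed inputs (not in the article)**
- ICC from 0.01 to 0.20.
- r of 0.3, 0.5 or 0.7.
- A true effect of 0.5 SD.
- Equal SD and ICC at both time points.
- Equal home sizes.

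**Formulas**, for a quantitative score in SD units:
- Unadjusted nine-month comparison: V = 2[1 + (m − 1)ICC]/(8m).
- Adjusted for baseline: V(1 − r²).
- Change score: V × 2(1 − r).
- Correlation of home means: r = [m·ICC·(home-level correlation) + (1 − ICC)·(resident-level correlation)]/[1 + (m − 1)ICC].
- Power from the noncentral t. Between-home degrees of freedom are 16 − 9 = 7 for the full factorial plus replication, or 16 − 5 = 11 for main effects plus replication. The adjusted model is charged one fewer.

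**Worked case, ICC 0.05.** V = 2 × (1 + 11 × 0.05)/96 = 3.10/96 = 0.0323, so the unadjusted SE is 0.180. At r = 0.5 the adjusted variance is 0.0323 × 0.75 = 0.0242, SE 0.156.

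| r | Variance removed | SE unadjusted | SE change score | SE adjusted | Effect detectable at 80% power, unadjusted → adjusted | Power for 0.5 SD, unadjusted → adjusted |
|---|---|---|---|---|---|---|
| 0.3 | 9% | 0.180 | 0.213 | 0.171 | 0.59 → 0.58 SD | 67% → 68% |
| 0.5 | 25% | 0.180 | 0.180 | 0.156 | 0.59 → 0.52 SD | 67% → 76% |
| 0.7 | 49% | 0.180 | 0.139 | 0.128 | 0.59 → 0.43 SD | 67% → 90% |

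(7 df unadjusted and for change scores, 6 df adjusted.)

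**Sensitivity**, power for 0.5 SD:
- ICC 0.10, 7 df: 54% unadjusted; 56%, 64% and 80% adjusted at r = 0.3, 0.5 and 0.7.
- ICC 0.20, 7 df: 39% unadjusted; 40%, 47% and 62% adjusted.
- ICC 0.05, 11 df: 72% unadjusted; 75%, 82% and 94% adjusted.

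**Adjusted against change scores.** The variance ratio is (1 − r²)/[2(1 − r)] = (1 + r)/2, which is 0.65, 0.75 and 0.85 at the three values of r and never exceeds 1. Change scores are worse than no adjustment at r = 0.3 (0.213 against 0.180) and close to the adjusted analysis at r = 0.7 (0.139 against 0.128).

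The formulas are for quantitative scores. For antipsychotic use as yes or no, the gain would depend on prevalence and continuation rates that the article does not give, so no figure is claimed.

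**The case against.** The strongest reply is that a condensed article is being read too closely. It says the analysis will involve an ANOVA and defers detail to a later analysis plan, where covariates and subgroup terms commonly sit. The response is undefined, so change scores, which do use baseline, would fit the text. The trial is a pilot with no power claim, and every figure above rests on assumed correlations.

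Much of this stands. It rules out four stronger readings that a reader might infer:
- **That the article decides to ignore baseline.** It does not say outcomes will be unadjusted. It names a model and its terms and leaves baseline out.
- **That the unadjusted analysis is biased.** Randomisation keeps it unbiased in expectation, and the standard error of a multilevel model already allows for chance differences between homes.
- **That hypothesis 2 cannot be answered.** The social interaction factor tests its main claim. Baseline CMAI is collected, so the baseline-dependent clause can be examined; the article simply links no analysis to it, and that is mainly detail for the analysis plan.
- **That an inflated residual variance feeds WP5 planning.** The article names baseline SDs and overall effect sizes for that purpose. A baseline SD does not depend on the outcome model.

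The reply does not dispose of the point. The article goes beyond silence: it fixes a model class, factors, replication and clustering, and an analysis plan written to match would be an ANOVA. The change-score reading does not rescue it either, because baseline adjustment is at least as precise throughout.

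**Conclusion.** The point holds as a matter of efficiency and specification. The stated model has no baseline term where ten of eleven outcomes have a baseline value and each contrast rests on 8 homes against 8. A better method is available with data already collected.

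The size depends on r, which the documents do not give. The variance of each main effect falls by about 9%, 25% or 49% at r = 0.3, 0.5 or 0.7. At 0.3 the gain is nearly cancelled by the lost degree of freedom; from about 0.5 it is material. These figures assume equal home sizes, equal SDs and ICCs over time, and quantitative scores. No stated number in the article is wrong, and the pilot's validity is not in question.

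**What to change.** State the outcome model as a multilevel ANCOVA:
- Response: the nine-month value.
- Covariate: the resident's baseline value of the same measure, with the home's baseline mean added if home-level and resident-level relations may differ. For QUIS, use the home's baseline score. For falls, use none.
- Keep the three factors and replication as fixed terms and home as random.
- Test the factors on between-home degrees of freedom, for example with Kenward-Roger.

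As a secondary, exploratory item, name one baseline CMAI by social interaction term for the baseline-dependent clause of hypothesis 2.

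The cost is a change of wording in the protocol and analysis plan, with no new data. At most one between-home degree of freedom is lost if the home baseline mean is added: 7 to 6 with the full factorial, or 11 to 10 with main effects only.

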### Qualitative data management and analysis

All group discussions will be audio-recorded and transcribed verbatim. A systematic analysis procedure, based upon the principles of grounded theory, will be used to generate increased understanding of the implications of care staff attitudes for the implementation of the interventions. The aim of the analysis will be to increase the level of abstraction of themes from descriptive to interpretive. The procedure will involve at least two members of the research team independently indexing sections of the transcriptions with descriptive codes. These codes will then be organised into more abstract categories and the links between these categories identified. The categories generated in the last stage (theoretical coding) are expressed as hypotheses or propositions. Constant comparison and negative case analysis will be applied to the data from different settings to increase understanding of the processes underlying response to the interventions. Findings of the qualitative study will contribute to the optimization of the interventions, the training and the implementation approaches in the larger RCT, WP5. The qualitative study may also shed more light on specific outcomes and mediators (working mechanisms) of the interventions, as described previously. These considerations will need to be taken into account in the planned RCT.

